| FACIT-Score                                                              | x                                                                                | x              | x              | x              | x              | x              | x              | x              | x                                            |
| SLICC Damage Index                                                       |                                                                                  |                |                |                |                |                |                |                | x                                            |
| Safety Evaluations                                                       |                                                                                  |                |                |                |                |                |                |                |                                              |
| Physical exam                                                            | x                                                                                | x              | x              | x              | x              | x              | x              | x              | x                                            |
| Vital signs                                                              | x                                                                                | x              | x              | x              | x              | x              | x              | x              | x                                            |
| ECG                                                                      | x                                                                                |                |                |                |                |                |                |                | x                                            |
| SARS-CoV-2 Rapid-Test ###                                     | x                                                                                | x              | x              | x              | x              | x              | x              | x              | x                                            |

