### 3.1.5 SECONDARY OBJECTIVES OF THE LTE OBSERVATIONAL PERIOD

1. To evaluate the long-term efficacy of daratumumab, previously administered in the core study period, for the treatment of SLE by means of SLEDAI-scores, CLASI scores, CDAI scores, SELENA-SLEDAI Flare Index (SFI) and attainment of SRI-4 or LLDAS responses
2. To investigate the long-term serologic changes of anti-dsDNA antibodies and other autoantibodies present at baseline of the core study, and total immunoglobulin levels in serum
3. To assess the long-term health outcome measures (SF-36, FACIT scores)
4. To investigate the damage accrual according to SLICC Damage Index (SDI)

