- The daily prednisolone (or equivalent) dosage, by visit between Week 12 and Week 36. Time frame: baseline, and follow-up visits of the core study period at Week 3, 5, 7, 9, 12, 16, 20, 24, 28, 32, 36, and each follow-up visit of the LTE observational period.  
Time to new treatments to control lupus activity will be investigated. Time-frame: baseline, and follow-up visits of the core study period at Week 3, 5, 7, 9, 12, 16, 20, 24, 28, 32, 36, and at Week 42, 48, 54, 60, 66, 72, 78 and 84 of the LTE observational period.

4. To evaluate whether daratumumab treatment is associated with improvement of health-related quality of life, the following outcome measures will be performed:

- Change from baseline in Health-related quality of life (HR-QoL), measured by SF-36 score, time frame: up to Week 36. The 36-Item Short Form Health Survey questionnaire (SF-36), a validated instrument widely used to evaluate Health-Related Quality of Life SLE, by visit. Time frame: baseline, and follow-up visits of the core study period at Week 3, 5, 7, 9, 12, 16, 20, 24, 28, 32, 36, and at Week 42, 48, 54, 60, 66, 72, 78 and 84 of the LTE observational period.
- Change from baseline in Functional Assessment of Chronic Illness Therapy (FACIT)-Fatigue score. Time frame: up to Week 36. The FACIT-Fatigue scale includes 13-fatigue related questions for subject rates fatigue during the previous 7 days, yielding on overall score 0 to 52, with lowest score representing worst fatigue, by visit. Time frame: baseline, and follow-up

visits of the core study period at Week 3, 5, 7, 9, 12, 16, 20, 24, 28, 32, 36, and at Week 42, 48, 54, 60, 66, 72, 78 and 84 of the LTE observational period.

- Change from screening in the number of organs with damage according to the SLICC Damage Index (SDI) measured at the final visit at Week 84

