In the event of withdrawal from the study through a decision by the sponsor, the investigating doctor or the study participant, the early termination visit will be carried out (which is equivalent to the visitation procedures at Week 36 of the core study period or Week 84 in the LTE observational period). Furthermore, a follow-up visit will be held, recording the adverse outcomes with an interval of 8 weeks after the last administration of the study drug (final study visit). The participants in the study will be transferred for further rheumatological treatment to the respective responsible/referring treatment institution after the study has been concluded.

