### 9.4 MISSING VALUES

Missing values in primary and secondary outcome measures will be replaced by the last known value of any previous assessment (LOCF principle) for the primary analyses. Missing data for safety endpoints will not be replaced.

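### SDI damage endpoint: reference visit and schedules do not agree, and LOCF enters patients with only a baseline SDI as exactly zero damage accrual

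*Protocol*

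**What the plan says.** Damage accrual measured by SDI is a secondary objective of the LTE (Protocol, Section 3.1.5). The matching endpoint in Section 3.2.3 has one time point and one reference: "Change from screening in the number of organs with damage according to the SLICC Damage Index (SDI) measured at the final visit at Week 84".

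Four tables schedule the "SLICC Damage Index":
- Both core tables (front Time and events schedule; Section 7.1.1) mark it at baseline only. Screening and Week 36 are blank.
- The LTE table in the front schedule marks it at Week 84 only.
- The LTE table in Section 7.1.1 marks it in all nine columns, Weeks 36 to 84.

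Three rules decide what happens to patients without a Week 84 value:
- Section 9.3 puts all enrolled patients in the main analyses of primary and secondary outcomes, with a complete case analysis as sensitivity analysis.
- Section 9.4: "Missing values in primary and secondary outcome measures will be replaced by the last known value of any previous assessment", that is, LOCF.
- Section 8.3 provides an early termination visit, "which is equivalent to the visitation procedures at Week 36 of the core study period or Week 84 in the LTE observational period". It is triggered "In the event of withdrawal from the study through a decision by the sponsor, the investigating doctor or the study participant".

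Entry to the LTE needs written consent (Section 5.3). Section 7.3.8 describes SDI damage as irreversible and present for at least 6 months.

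**The concern.** Three parts of the plan do not fit together. The endpoint refers to a screening value that no table schedules. The two LTE tables give sites different instructions, including whether SDI is scored at Week 36. The general LOCF rule then applies to an outcome for which some patients will have only a baseline score.

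For those patients LOCF copies baseline to Week 84, so the change is exactly 0. Because the index counts irreversible damage, zero change is the most favourable value a patient can have. The error therefore runs in one direction: it can understate damage accrual and cannot overstate it. In a trial of 10 patients each forced zero is 10% of the analysed data.

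**Working it through.** **1. The schedules side by side**

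| Visit | Front schedule | Section 7.1.1 |
|---|---|---|
| Screening | no SDI | no SDI |
| Baseline | SDI | SDI |
| Week 36, core table | no SDI | no SDI |
| Week 36, LTE table | no SDI | SDI |
| Weeks 42, 48, 54, 60, 66, 72, 78 | no SDI | SDI |
| Week 84 | SDI | SDI |

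The LTE tables have 9 visits (Weeks 36 to 84). The front table marks 1 and Section 7.1.1 marks 9, so they differ at 9 − 1 = 8. Section 7.1.1 also disagrees with itself at Week 36 (visit 17): blank in its core table, marked in its LTE table.

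**2. Who has a post-baseline SDI**

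| Patient | Front LTE table governs | Section 7.1.1 LTE table governs |
|---|---|---|
| Withdraws in the core period, attends termination visit (core Week 36 procedures) | none | none on the core table; unclear whether the LTE table's Week 36 mark applies |
| Completes Week 36, does not enter the LTE | none | unclear, same reason |
| Withdraws in the LTE, attends termination visit (Week 84 procedures) | yes | yes |
| In the LTE, lost to follow-up or dead before Week 84 | none | yes, from Week 36 on |
| Reaches Week 84 | yes | yes |

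Loss to follow-up and death are listed in Section 8.3 as reasons for withdrawal, but the termination visit is provided for withdrawal decided by the sponsor, the investigator or the participant.

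**3. What LOCF does where the table says none**

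Change = carried-forward value − baseline value = baseline − baseline = 0.

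**4. Size**

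The protocol states no sample size, power or expected accrual for SDI, so there is no SDI figure to reproduce. The planning drop-out in Section 9.2 does reproduce: 5/(1 − 0.5) = 10 enrolled.

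Let k of the 10 patients have only a baseline SDI, and assume accrual is unrelated to stopping. The expected estimate (mean accrual, or proportion with any accrual) is then

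estimate = true value × (10 − k)/10.

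The documents give no accrual rate, so a true proportion of 5% to 30% is an assumption used to show the range.

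| k | Factor | Estimate if truth is 5% | Estimate if truth is 30% |
|---|---|---|---|
| 1 | 0.9 | 4.5% | 27% |
| 2 | 0.8 | 4% | 24% |
| 3 | 0.7 | 3.5% | 21% |
| 5 | 0.5 | 2.5% | 15% |

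The row k = 5 applies only if the full 50% planning drop-out (0.5 × 10 = 5) falls in the groups without a post-baseline SDI.

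**5. What earlier scoring could add**

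Taking 6 months as about 26 weeks, an SDI at Week 36 can count only new damage that began by about Week 36 − 26 = 10. A termination visit before about Week 26 cannot count damage that began after baseline.

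**The case against.** A reader might infer that everyone who stops before Week 84 lacks a second SDI, so that the share not reaching Week 84 equals the share of forced zeros. The documents do not support this. The termination rule in Section 8.3 gives LTE withdrawals the Week 84 procedures, and both LTE tables mark SDI at Week 84. If the LTE table in Section 7.1.1 governs, anyone scored from Week 36 on also has a value.

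A reader might also infer that only the patients doing best are measured. Nothing shows that either. Section 5.3 sets no response criterion for LTE entry, and Sections 7.2.3 and 8.2 keep treatment failures and patients who stop the drug in the study.

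Nor does the protocol imply 5 forced zeros of 10. Its 50% is a planning figure for the Week 12 comparison.

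Other points stand in part:
- The planned complete case analysis would show how much the fill-in matters. It is a sensitivity analysis, though, and LOCF remains the primary method.
- A single late SDI is defensible given the 6-month requirement, and some early zero changes would arise from the instrument itself.
- SDI is one of many secondary endpoints in an exploratory single-arm trial, and no decision rule depends on it.
- The analysis plan, which is not at hand, might restrict SDI to LTE entrants. The two core groups would then drop out of the problem. The protocol as written includes all enrolled patients.

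**Conclusion.** The point holds in limited form. The mismatch between the screening reference and the baseline-only scoring, and the conflict between the LTE tables at 8 of 9 visits, are plain inconsistencies in the current text. The first is mainly one of wording, since a pre-treatment score does exist at baseline. The second leaves sites without a clear instruction at Week 36.

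The statistical consequence is a one-directional understatement of damage accrual. It is confined to core withdrawals, to core completers outside the LTE (unless Section 7.1.1's Week 36 mark covers them), and, under the front table only, to LTE patients lost to follow-up or dead. Its size is the factor (10 − k)/10, with k unknown in advance. This rests on LOCF being applied as Section 9.4 states in all enrolled patients, and on accrual being unrelated to stopping. If patients who stop accrue more damage than the others, the understatement is larger. The primary endpoint is not touched.

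**What to change.** 1. Make the SDI rows of the two LTE tables agree, and make the Week 36 column say the same in the core and LTE tables.
2. In Section 3.2.3, refer the change to baseline instead of screening.
3. Exempt SDI from Section 9.4. Report SDI change as observed, with the number of patients who have a post-baseline score and the visit at which it was taken.

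These are text changes at no cost in visits or data. Scoring SDI at Week 36 and at core early termination would be an optional addition: one short physician form at visits that already take place. Its yield is limited by the 6-month requirement, so it does not replace step 3.

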| SLE classification (2019 EULAR/ACR criteria)      | x         |          |          |    |    |    |    |    |    |    |                     |         |     |     |     |     |                             |
| QuantiFERON-TB                                    | x         |          |          |    |    |    |    |    |    |    |                     |         |     |     |     |     |                             |
| Viral Serology                                    | x         |          |          |    |    |    |    |    |    |    |                     |         |     |     |     |     |                             |
| Screening SLE Serology for SLEDAI-2K              | x         |          |          |    |    |    |    |    |    |    |                     |         |     |     |     |     |                             |
| SLICC Damage Index                                |           | x        |          |    |    |    |    |    |    |    |                     |         |     |     |     |     |                             |
| Study Treatment Administration                    |           |          |          |    |    |    |    |    |    |    |                     |         |     |     |     |     |                             |
| Dispense/administer study drug                    |           | x        | x        | x  | x  | x  | x  | x  | x  |    |                     |         |     |     |     |     |                             |
| Clinical Response Evaluations                     |           |          |          |    |    |    |    |    |    |    |                     |         |     |     |     |     |                             |
| SLEDAI-2K                                         | x         | x        | x        |    | x  |    |    | x  |    | x  | x                   | x       | x   | x   | x   | x   | x                           |
| Physician's Global Assessment of Disease Activity | x         | x        | x        |    | x  |    |    | x  |    | x  | x                   | x       | x   | x   | x   | x   | x                           |
| BILAG                                             | x         | x        | x        |    | x  |    |    | x  |    | x  | x                   | x       | x   | x   | x   | x   | x                           |

|                                                                     |   |   |     |     |     |     |     |     |     |     |     |     |     |     |     |

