### 7.3.8 SLICC Damage Index (SDI)

The change in accumulating organ damage will be investigated using the ACR/SLICC Damage Index (SDI). The SDI was developed to quantify damage that has occurred since onset of lupus. It has been shown to be a valid measure for damage and correlates with mortality. In this index, damage is defined a non-reversible change, not related to active inflammation, occurring since the onset of lupus, ascertained by clinical assessment and present for at least 6 months

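### The SDI endpoint counts damaged organs, so further damage in an organ already damaged at entry adds nothing to the accrual it is meant to measure, and the 6-month rule blurs both ends of the window

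*Protocol*

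**What the plan says.** - **Objective (Protocol 3.1.5, LTE secondary objectives):** "To investigate the damage accrual according to SLICC Damage Index (SDI").
- **Endpoint (Protocol 3.2.3):** "Change from screening in the number of organs with damage according to the SLICC Damage Index (SDI"), with Week 84 as the closing assessment. It stands as the last bullet under health-related quality of life.
- **Definition (Protocol 7.3.8):** "The change in accumulating organ damage will be investigated using the ACR/SLICC Damage Index (SDI"). Damage is a non-reversible change, not due to active inflammation, "occurring since the onset of lupus", and it must be "ascertained by clinical assessment and present for at least 6 months". The section gives no rule for calculating a score.
- **Schedule:** the Time and events schedule and section 7.1.1 both place the first "SLICC Damage Index" assessment in the Baseline column (Day 0), with none at screening. For the LTE period they differ: the Time and events schedule shows Week 84 only, and section 7.1.1 shows every visit from Week 36 to Week 84.

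**The concern.** The quantity analysed is not the quantity that the objective names. Accrual means damage that builds up. A count of affected organs records only the first damage in each organ. The study enrols patients who have failed or not tolerated at least two drugs, so damage at entry is plausible, although the protocol does not give its frequency. Patients with such damage are the ones whose further progression the count can miss.

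The second issue is timing. Because damage must have lasted 6 months, each assessment describes lesions that began at least 6 months earlier. The change between the two visits therefore covers an onset period that starts before the first dose and ends well before Week 84. The study is uncontrolled, so no comparison arm offsets this shift when the result is read as what happened after daratumumab.

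**Working it through.** The plan states no figure for this endpoint, so there is none to reproduce. The check covers the logic of the count and the arithmetic of the 6-month rule.

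**Inputs**
- Unit counted, reference and end point: organs, screening, Week 84 (3.2.3).
- Minimum duration of damage: 6 months (7.3.8), taken as 182.6 days.
- First SDI assessment: Day 0 in both core schedules. Screening runs up to 28 days before that.
- Day of Week 84: the LTE tables print no days. Extending the core convention (Week 1 = Day 0) gives 7 x (84 - 1) = Day 581.
- Visit window at Week 84: plus or minus 14 days.

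**Step 1: the organ count.** Score an organ 1 if damaged and 0 if not. Damage is non-reversible by definition.
- Damaged at entry and at Week 84: 1 - 1 = 0, however much damage was added.
- Undamaged at entry, damaged at Week 84: 1 - 0 = 1, however much damage occurred.

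**Step 2: which onsets count as new.** A lesion counts at a visit on day V only if its onset is no later than V - 182.6. It is new at Week 84 if its onset lies after (reference day - 182.6) and no later than (Week 84 day - 182.6), and its organ was not already counted. Damage that is at least 6 months old at the reference visit is in both counts and cancels.

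**Step 3: the window**
- Latest onset that can count: 581 - 182.6 = Day 398.4, and 398.4/7 + 1 = Week 57.9.
- Part of the time after first dose that cannot contribute: 182.6/581 = 31.4%.
- Reference at Day 0: the window runs from Day -182.6 to Day 398.4, which is 581 days. The part before first dose is 182.6/581 = 31.4%.
- Reference at screening, Day -28: the window runs from Day -210.6 to Day 398.4, which is 609 days. The part before first dose is 210.6/609 = 34.6%.

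**Step 4: sensitivity**
- Week 84 visit 14 days early (Day 567): cut-off Day 384.4; missed share 182.6/567 = 32.2%; pre-dose share 32.2% (Day 0) or 210.6/595 = 35.4% (Day -28).
- Week 84 visit 14 days late (Day 595): cut-off Day 412.4; missed share 182.6/595 = 30.7%; pre-dose share 30.7% (Day 0) or 210.6/623 = 33.8% (Day -28).
- The core schedule prints Day 241 for Week 36, where the convention gives 7 x 35 = 245. Counting 48 weeks from Day 241 gives 241 + 336 = Day 577, a cut-off of Day 394.4 and a missed share of 182.6/577 = 31.6%. The conclusion does not change.

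**Step 5: weight of one organ.** With 10 patients, one organ wrongly counted or missed moves the mean change by 1/10 = 0.1. If only 5 remained, applying the 50% drop-out of section 9.2 to Week 84 as an illustration, it would move the mean by 1/5 = 0.2.

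**The case against.** Several points on the other side stand.

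- **The lag belongs to the definition of damage, not to the organ count.** An SDI score read at the same two visits has the same lag at both ends. Changing to a score addresses Step 1 only.
- **A reader might infer that any damage begun before the first dose is charged to the period after daratumumab.** The documents do not support that. Damage at least 6 months old at the first assessment cancels, and younger damage enters only through an organ not already counted.
- **A reader might infer that onset is ignored altogether.** That is also too strong. An assessor must judge approximate onset to apply the 6-month rule. Detailed dating rules could stand in the SAP or the CRF, which are not shown, so their absence from the protocol is not a fault in itself.
- **The protocol gives no SDI scoring rule.** How a total behaves within one organ cannot be checked from it. The finding therefore rests on the mismatch between an organ count and an accrual objective.
- **Serial scoring would help.** If the SDI is scored at every LTE visit, as in section 7.1.1, damage first scored after Week 36 can be dated approximately. The Time and events schedule does not provide for this.
- **The stakes are low.** The endpoint is missing from the synopsis and is not named in section 9.5.2. The objective and endpoint promise a change, not attribution to the drug.

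None of this removes the organ-count problem, because the protocol's own endpoint wording fixes the unit.

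**Conclusion.** The concern holds as a minor point. As written, the endpoint cannot register further damage in an organ that is already damaged at entry, which does not fit the accrual objective. This follows from the wording alone and needs no assumption about rates.

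The timing effect is real but limited. It concerns lesions less than about 6 months old at the first SDI assessment (back to about Day -183, or Day -211 if the reference is screening at Day -28) and lesions that begin after about Day 398. It assumes that the 6-month rule is applied as stated and that the lesions persist.

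The 31% to 35% figures are shares of calendar time. A reader might take them to mean that about a third of reported accrual is misplaced. That would require onset to be uniform over time, and the protocol gives no damage incidence to support it.

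**What to change.** 1. Define the endpoint in section 3.2.3 as the change in SDI score from the baseline assessment to Week 84, with the number of patients with any increase. State the scoring rule in section 7.3.8. The organ count may stay as a supplementary description.
2. Use baseline as the reference instead of screening, since both core schedules place the SDI at baseline. Reconcile the two LTE schedules on the SDI visits at the same time.
3. Record an approximate onset date for each SDI item. As a descriptive supplement, and not as an exclusion from the score, list separately the items that began before the first dose and the lesions not yet 6 months old at Week 84.

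The cost is a change of wording and one extra CRF field per SDI item. The baseline and Week 84 assessments are already scheduled, so no visit or test is added.
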